## Abstract

**Background:**

Global trends in cardiovascular disease (CVD) exhibit considerable interregional and interethnic differences, which in turn affect long-term CVD risk across diverse populations. An in-depth understanding of the interplay between ethnicity, socioeconomic status, and CVD risk factors and mortality in a contemporaneous population is crucial to informing health policy and resource allocation aimed at mitigating long-term CVD risk. Generating bespoke large-scale and reliable data with sufficient numbers of events is expensive and time-consuming but can be circumvented through utilization and linkage of data routinely collected in electronic health records (EHR).

**Objective:**

We aimed to characterize the burden of CVD risk factors across different ethnicities, age groups, and socioeconomic groups, and study CVD incidence and mortality by EHR linkage in London.

**Methods:**

The proposed study will initially be a cross-sectional observational study unfolding into prospective CVD ascertainment through longitudinal follow-up involving linked data. The government-funded National Health System (NHS) Health Check program provides an opportunity for the systematic collation of CVD risk factors on a large scale. NHS Health Check data on approximately 200,000 individuals will be extracted from consenting general practices across London that use the Egton Medical Information Systems (EMIS) EHR software. Data will be analyzed using appropriate statistical techniques to (1) determine the cross-sectional burden of CVD risk factors and their prospective association with CVD outcomes, (2) validate existing prediction tools in diverse populations, and (3) develop bespoke risk prediction tools across diverse ethnic groups.

**Results:**

Enrollment began in January 2019 and is ongoing with initial results to be published mid-2021.

**Conclusions:**

There is an urgent need for more real-life population health studies based on analyses of routine health data available in EHRs. Findings from our study will help quantify, on a large scale, the contemporaneous burden of CVD risk factors by geography and ethnicity in a large multiethnic urban population. Such detailed understanding (especially interethnic and sociodemographic variations) of the burden of CVD risk and its determinants, including heredity, environment, diet, lifestyle, and socioeconomic factors, in a large population sample, will enable the development of tailored and dynamic (continuously learning from new data) risk prediction tools for diverse ethnic groups, and thereby enable the personalized provision of prevention strategies and care. We anticipate that this systematic approach of linking routinely collected data from EHRs to study CVD can be conducted in other settings as EHRs are being implemented worldwide.

**International Registered Report Identifier (IRRID):**

PRR1-10.2196/17548

## Introduction

### Background

Globally, cardiovascular disease (CVD) is a leading cause of disability and premature mortality, with the number of deaths attributable to CVD rising from 12.3 to 17.3 million between 1990 and 2013 [1]. Furthermore, projections indicate that CVD will remain the leading cause of mortality worldwide for decades [2]. Notwithstanding the public health importance of CVD and its risk factors, the use of proven preventative strategies to mitigate risk is far from satisfactory due to a multitude of factors including complex intra- and interregional distribution of the determinants of CVD [1,3]. For instance, deaths attributable to different types of CVD vary between China and the United Kingdom. This variation may, in part, reflect the prevalence of different underlying risk factors such as hypertension and diabetes [4]. Thus, with regions around the world undergoing major epidemiological transitions, a population strategy aimed at reducing the burden of classical risk factors can have a major impact on CVD risk reduction [5].

### Population Prevention Strategy in England

In England, the National Health Service (NHS) established a population-based Health Check program in 2009 to provide a systematic assessment and management of CVD risk for adults. Individuals aged 40-74 years without pre-existing CVD, diabetes, or hypertension are invited for a five-yearly check-up to identify and to receive advice and treatment for their risk of having a CVD event [6]. Commissioned by local authorities and delivered primarily through primary care practices, henceforth referred to as general practices (GP), this program aims to prevent around 2000 deaths and 9500 nonfatal myocardial infarctions (MI) and strokes annually [7,8]. As a free service for all eligible individuals, this program has the potential to reduce health inequalities associated with CVD [7,8], assuming equitable uptake and universal coverage. Available data suggest that between 2011-12, NHS Health Check coverage in east London was quite high at 73% (compared to national coverage of 30%). Of those that attended the screening, over a third belonged to ethnic minority groups such as south Asians and Black African/Caribbeans [9-13]. While modification of individual risk factors (eg, blood pressure) has generally been shown to be associated with improved health outcomes (eg, lower incidence of ischaemic stroke), favorable changes in risk factor distribution at a societal level have also contributed to overall improvements in community health [14]. For example, in 1989, in Poland, the increased accessibility and consumption of fruits and vegetables through the opening of markets resulted in a reduction in CVD mortality [15]. By contrast, Japanese migrants, who adopted the diet and lifestyle of the United States (US) population, relative to those who retained their original dietary patterns, had a higher prevalence of CVD [16]. Given the variation in ethnic-specific diet and lifestyle habits, and given genetic differences across population groups around the world, there is currently an unmet need to understand the complex relationship between ethnicity and factors as diverse as heredity, environment, diet, lifestyle, and socioeconomic factors (and their mutual interaction) in determining the burden, distribution, and temporal trends in both CVD risk factors and clinical CVD outcomes and cause-specific death.

Dietary exposures determine nutritional status, which may, in turn, impact CVD outcomes. As nutritional status is a key intermediary in the development of CVD, health services need to measure nutritional status as well as associated dietary exposures in order to guide appropriate preventative measures, particularly in multiethnic populations in primary care. The National Diet and Nutrition Survey (NDNS) and components of the National Survey of Health and Development (NSHD) have been developed to assess dietary exposure patterns, nutritional status, and associated social as well as biological factors within a sample of UK populations [17-19]. However, to date, no systematic attempts have been made to harness these data to boost or complement information gleaned from population-based studies investigating ethnic-specific CVD risk factor burden or risk [20].

### Calculation of CVD Risk

The risk of CVD in an asymptomatic individual is based on risk factor data collected by their primary care physician to produce a numerical estimate. Traditional risk scores, such as those derived from the Framingham risk equation, have potential limitations, primarily because they were derived from a cohort of predominantly White individuals in the United States [21,22]. Moreover, they do not make allowances for factors such as socioeconomic status, resulting in systematic over- or underestimation of CVD risk based on the population studied [21,22]. With the emergence of obesity and diabetes as key global cardiovascular risk factors [22], the QRISK2 CVD risk calculator was developed and calibrated, enabling adjustments for more contemporary risk factors in the United Kingdom [22,23]. Despite these considerations, the representation of ethnic minorities in the cohort used to derive QRISK2 was approximately 1% for South Asians and 0.5% for Afro-Caribbean individuals, with the likelihood of underestimation of 10-year CVD event risk in these population groups [21].

Furthermore, QRISK prediction models contain imputations due to missing data. While established statistical methods are often used, considerations such as imputing cholesterol values to individuals without vascular disease could lead to weakened associations between cholesterol and CVD [24], as was observed in the first iteration of QRISK where about 80% of cholesterol measures were imputed. Hence, additional validation of QRISK2 in a contemporaneous multiethnic population with more systematic approaches to the collation of exposures than previously possible would be beneficial [21].

These systems need to be interoperable to enable a systematic analysis of routine healthcare data collected in electronic health records (EHRs). However, over 100 commercial EHR vendors are operating within the NHS across primary, secondary, and tertiary sectors [25]. While organizations are beginning to link data from different EHR systems, there is still fragmentation and absence of vital data as, for example, GPs serving multiethnic populations are not providing their data. Moreover, given that establishing bespoke prospective studies on CVD prevention can be prohibitively expensive, using real-life routinely collected data from EHRs and subsequent linkage of these datasets across different sectors can provide invaluable systematic approaches to conducting research.

We developed the following study specific objectives:

To robustly quantify and characterize, across diverse ethnic groups and sociodemographic groups, the burden of CVD risk factors among NHS Health Check attendees in a diverse population in London.To prospectively study the incidence of CVD within this population by EHR linkage.To validate existing CVD risk prediction algorithms and to develop novel, bespoke algorithms for CVD risk prediction among diverse multiethnic population groups.To characterize dietary exposures and nutritional status as well as their associations with CVD outcomes, using data from index assessment methods that mirror or correlate well with those used in national surveillance.

## Methods

### Study Design and Setting

We propose to conduct a large-scale, cross-sectional observational study of NHS Health Check attendees in London with additional virtual longitudinal follow-up established via electronic health record linkage of their primary (NHS Health Check) and secondary care (hospital) data over 10 years starting in 2009. One of the major providers of EHR software to GP practices is Egton Medical Information Systems (EMIS). GPs utilizing this EHR will be eligible to participate. Figure 1 illustrates the number of individuals belonging to ethnic minority groups within London. Such a high prevalence of diverse ethnic groups in London, relative to other areas in England, coupled with high utilization of the EMIS system (Figure 2), lends itself naturally to London as the ideal backdrop for our proposed investigation.

**Figure 1 figure1:**
[figure not shown]
Data from 2011, showing ethnic minority populations across the regions of England [26].

**Figure 2 figure2:**
[figure not shown]
Map of London showing the number of GP practices utilizing the EMIS system (red), boroughs utilizing EMIS (asterisk), and proportion of Black and Minority Ethnic (BME) by region [26-36].

### Recruitment

GP practices using EMIS Web clinical systems across London will be invited to provide practice-wide consent to participating in the study by way of sharing pseudonymized data on individuals undergoing NHS Health Checks within their practices between 2009 and 2018. GP practices across London are being informed of the study and recruited through liaising with clinical research networks through information letters and Clinical Commissioning Group meetings. Data will be remotely extracted centrally by EMIS using Read codes.

### Data Collection and Linkage

Our study, designed as a population-based registry at the outset, will collect, alongside NHS Health Check data, additional demographic variables and prescription information to help build a large and robust repository of primary care data on residents of London undergoing NHS Health Check from 2009 onwards in GP practices.

All individuals seeking healthcare in the United Kingdom are assigned a unique identifier (ie, their NHS number). This number allows the allocation of any subsequent data collected to the individual’s record and enables linkage with diverse data sources. For instance, the Office for National Statistics and Hospital Episode Statistics databases maintain records on mortality and clinical outcomes of individuals utilizing secondary healthcare services, respectively. Data from these sources can be linked through NHS numbers to the NHS Health Check data to provide a comprehensive and contemporary database on CVD risk factors (predictor variables) and outcomes across different ethnic groups. Other data sources recording clinical CVD outcomes such as the Myocardial Infarction National Audit Project and the National Institute of Cardiovascular Outcomes Research will also be harnessed to provide additional details relevant to this study.

This process of data sharing and linking, while protecting an individual’s confidentiality, is possible due to pseudonymization and will be conducted by EMIS and a third party organization familiar with bespoke linkage. Using Open Pseudonymiser Software, EMIS will create a pseudonymized version of NHS numbers for individuals who meet the inclusion criteria. The data will be encrypted with a project-specific key. By using this encrypted key, an external organization will be able to link the NHS Health Check data with outcomes data through a similar pseudonymization process and a Global Unique Identifier (GUID). The research team will only have access to completely linked anonymized data as the linkage of NHS Health Check data with outcomes data will not contain the GUID.

### Sample Size

Although data are not available for 2009-2011, of the invited population for NHS Health Check in 2016-17, 51.6% and 49.9% were residing in London and the rest of England, respectively [27]. In 2015, EMIS utilization in GP clinics was approximately 55%. Therefore, if 50% of all NHS Health Check attendees visit GP clinics utilizing the EMIS system, then it can be assumed that 587,273 individuals in London are eligible for consideration in this study between 2011 and 2017 [28,29]. Due to a lack of visibility of the true number of GP practices using a particular system, Figure 2 highlights that the majority of the areas in London do utilize the EMIS system, and, therefore, we anticipate that the intended sample size will be met.

To develop novel risk prediction tools for population groups, we anticipate that data will be available on approximately 200,000 individuals across London between 2011 and 2017. During 2009-13, of those with a recorded ethnic group, uptake of the NHS Health Check across England was greatest amongst South Asians (19.2%), Black Caribbeans (19.6%), Black Africans (15.7%), and Chinese (15.3%). Attendance was 16.9% in all other recorded ethnic groups and 17.4% in white Caucasians. Extrapolating the current rate of CVD incidence (2.4%) for people aged below 79 years in England on our estimated study sample of 200,000, we expect to encounter 15,000 CVD events giving 100% power to observe relative risks as modest as 1.2-1.5 [23]. Within population subgroups, the power to detect overall association is expected to range from 49% to 100% [38,39]. Given the large Black and minority ethnic (BME) population in London and considering the above numbers, we estimate that our study sample will be highly representative of a diverse cohort [38,39].

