### Predictor and Outcome Variables

Cardiovascular risk factors (predictor variables) used to calculate QRISK2 include age, sex, ethnicity, index of multiple deprivations, smoking status, diabetes status, family history of CVD, chronic kidney disease (stage 4 or 5), atrial fibrillation, hypertension treatment, rheumatoid arthritis, lipids, blood pressure, and BMI. EMIS will also extract prescription data. CVD outcomes will include fatal and nonfatal coronary heart disease, fatal and nonfatal stroke, heart failure, all CVD-related hospitalizations (including those for revascularization), and all-cause mortality.

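### The 100% power for relative risks of 1.2-1.5 is stated without an exposed fraction or alpha, and does not hold for uncommon binary predictors at the lower end of that range

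*Protocol article*

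**What the plan says.** The Sample Size section applies an incidence of 2.4% to a sample of 200,000 and concludes: "we expect to encounter 15,000 CVD events giving 100% power to observe relative risks as modest as 1.2-1.5". It states no exposure, exposed fraction, alpha or sidedness. The one qualification is a power of 49% to 100% within population subgroups. That concerns smaller groups of people, not uncommon exposures in the whole cohort.

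The Statistical Analyses section plans Cox models for the association of individual risk factors with CVD outcomes. Predictor and Outcome Variables lists those factors. Several are binary, including diabetes status and "chronic kidney disease (stage 4 or 5), atrial fibrillation, hypertension treatment, rheumatoid arthritis". No prevalences are given.

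The section Population Prevention Strategy in England describes who enters the programme: "Individuals aged 40-74 years without pre-existing CVD, diabetes, or hypertension are invited".

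**The concern.** An event count alone does not fix the power for a binary predictor. The same 15,000 events carry much information about an exposure shared by a third of the cohort and little about one found in one person in 200. A single power figure for the whole range of relative risks therefore cannot cover every predictor on the list unless each is common enough.

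The article itself gives reason to doubt that for two of them. Diabetes status and hypertension treatment are listed as predictors, while the invited population is described as free of pre-existing diabetes and hypertension.

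What is at stake is how results are read. The Discussion again claims sufficient power on the strength of the sample size. If a reader takes 100% power to cover each listed factor, a non-significant result for an uncommon one looks like evidence of no association when the study may have had only a modest chance of detecting it.

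**Working it through.** **Inputs from the article.** Events D = 15,000; relative risks 1.2 and 1.5; sample 200,000; incidence 2.4% with no time unit; Cox regression.

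**Inputs assumed.** Alpha 5% two-sided; exposed fraction p between 0.1% and 50%; no loss of information from covariate adjustment.

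**Formula.** For a binary exposure, SE of the log hazard ratio = 1/√(D·p(1−p)), and power ≈ Φ(ln RR/SE − 1.96).

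**Reproducing the stated figure.** With D = 15,000 and p of 50%, 20% or 10%, power is 100.0% at both 1.2 and 1.5. The stated figure is right for exposures of that frequency.

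**One case in full (RR 1.2, p = 1%).** D·p(1−p) = 15,000 × 0.0099 = 148.5, with square root 12.19. Multiplying by ln 1.2 = 0.1823 gives 2.222. Then Φ(2.222 − 1.960) = Φ(0.262) = 60%.

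**Power with 15,000 events, by assumed exposed fraction:**

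| Exposed | RR 1.2 | RR 1.5 |
|---|---|---|
| 10% | 100% | 100% |
| 5% | 99.8% | 100% |
| 3% | 96.8% | 100% |
| 2% | 87.8% | 100% |
| 1% | 60.3% | 99.9% |
| 0.5% | 35.0% | 93.9% |
| 0.3% | 23.0% | 77.5% |
| 0.2% | 16.8% | 60.2% |
| 0.1% | 10.5% | 34.8% |

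**Thresholds.** Power that rounds to 100% means at least 99.5%, which requires p(1−p) ≥ (1.960 + 2.576)²/(D·(ln RR)²).

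- RR 1.2: 20.58/(15,000 × 0.03324) = 0.0413, so p ≥ 4.3%.
- RR 1.5: 20.58/(15,000 × 0.1644) = 0.0083, so p ≥ 0.84%.
- For 80% power the thresholds are 1.6% and 0.32%.

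**Sensitivity to method.** A one-sided 5% test at RR 1.2 gives 72% at 1% exposed and 47% at 0.5%. Comparing two proportions with 200,000 people and an overall risk of 7.5% (15,000/200,000) gives 70% and 44% at RR 1.2, and 100% and 98% at RR 1.5. The pattern is the same.

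**Dependence on the event count.** 2.4% × 200,000 = 4,800, whereas 15,000 is 7.5% of 200,000. The article gives no time unit or follow-up length to bridge the two. At 4,800 events the 99.5% thresholds become:

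- RR 1.2: 20.58/(4,800 × 0.03324) = 0.129, so p ≥ about 15%.
- RR 1.5: 20.58/(4,800 × 0.1644) = 0.0261, so p ≥ about 2.7%.

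Power at RR 1.2 and 1.5 would then be 78.6% and 100% at 5% exposed, and 24.1% and 79.8% at 1%.

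**The case against.** The strongest reply is that nothing has been miscalculated. The stated figure reproduces for any exposure of moderate frequency, and a condensed article may leave prevalence and alpha to the full protocol. Giving a range of relative risks may also mean that the detectable effect varies with the exposure. This stands in part: the arithmetic is sound for most exposures, and leaving out an input would not by itself be a finding. But the article does more than omit an input. It prints an unconditional result, and nothing in the text ties the lower end of the range to common exposures and the upper end to rarer ones.

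Three stronger readings are tempting, and the document does not support them.

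- A reader might infer that the claim holds only for common exposures. That goes too far: 5% exposed is enough at 1.2 and about 1% is enough at 1.5. At 1.5 the loss becomes material only below about 0.5%.
- A reader might infer that stage 4-5 kidney disease, atrial fibrillation and rheumatoid arthritis are shown to be underpowered. No prevalence is given for any of them, so this is an assumption.
- A reader might infer that predictors will be dropped when non-significant. No section plans selection by significance. The list is that of QRISK2, and predictive ability is judged by calibration, discrimination and reclassification.

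For diabetes and hypertension treatment the evidence is also incomplete. The invitation rule points to few exposed people at baseline but does not say how few. The Statistical Analyses section allows time-varying exposures and enters antihypertensive and antidiabetic prescribing as time-dependent covariates, so exposure can build up during follow-up.

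**Conclusion.** The concern holds in a limited form. The 100% power is stated without conditions and does not hold for every exposed fraction that the listed predictors could have. With 15,000 events it is correct at 1.2 from about 4.3% exposed and at 1.5 from about 0.84%. Below those levels the shortfall is mainly at the lower end of the range.

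The article supports low baseline exposure for diabetes status and hypertension treatment only, and does not show that either falls below a threshold. The figures rest on an assumed two-sided 5% alpha, an unadjusted binary exposure and the stated event count. Covariate adjustment would usually lower power further; this was not quantified, because no correlations are given. If the event count is nearer 4,800, the condition on exposure becomes considerably stricter.

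This is a matter of how the power is stated. It does not question the design or the planned models.

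**What to change.** Reconcile the event count first, giving the time unit of the 2.4% rate and the follow-up over which events are counted. Then replace the unconditional statement with one that names the relative risk, the exposed fraction and alpha. At 15,000 events and two-sided 5%, for example, it would read: at least 99.5% power at a relative risk of 1.2 when about 4.3% or more are exposed, and at 1.5 when about 0.84% or more are. At 4,800 events the corresponding figures are about 15% and 2.7%.

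For low-prevalence predictors, add a short table of the minimum detectable relative risk, exp[(z for alpha + z for power)/√(D·p(1−p))], using the prevalence found in the extract. A rule against dropping predictors for non-significance is not needed, since none is planned.

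The cost is a few sentences and a small table, with no new data and no change to the analyses. The stated power will look less favourable for uncommon predictors.

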Additional analyses will be conducted to quantify the impact of factors such as access to healthcare and utilization rates (of NHS Health Checks), prescription rates and medication compliance, and patterns of healthy behavior on CVD risk (both overall and, where possible, within subgroups). Standardized rates of prescription drug use will be calculated to investigate the extent of correlation between the present use of cardiovascular medication and cardiovascular risk. Variations in prescription patterns of CVD prevention and risk factor control, discontinuation of prescribed medication(s), and adverse effects to prescription medications from various therapeutic categories such as anti-hypertensive agents, lipid-lowering drugs (statins), and antidiabetic medication will be further assessed for their impact on CVD as time-dependent covariates in Cox regression models. Physical measurements within the NHS Health Check program will be obtained by the GP practices according to standard operating procedures, anticipating minimum inter-observer variability. Analyses to explore potential sources of heterogeneity concerning physical measurements (besides other characteristics) will also be conducted.

New and existing risk prediction models will be compared in terms of their ability to predict the onset of CVD across diverse population groups to develop improved risk prediction tools for primary prevention of CVD using outcomes data up to 2020. The resulting CVD risk algorithm will be calibrated by further analyses of CVD outcomes data of these patients through to 2027.

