As CVD burden varies between population groups and by regions, our study has the potential to investigate the expression of this disease and the contemporary risk factors in a large multiethnic cohort. Thus, our research can be considered a contemporary Framingham study on a large scale. Combining a real-life observational approach with the potential for yearly updates from the EHRs will offer new insights and understanding of the burden of risk factors for re-calibration of the variables used to derive risk prediction tools and dynamic improvement of risk prediction algorithms. Longitudinal follow-up will help quantify the incidence of CVD and, therefore, the derivation of population attributable risk (PAR) [44]. The ability to predict the impact of removing a particular risk factor in specific population groups and the risk of developing subsequent CVD is imperative for service provision and evaluating current public health strategies for CVD risk reduction. Thus, given its sample size, our study will have sufficient power to investigate CVD risk factor burden across diverse ethnicities among NHS Health Check attendees enabling further refinement of guidelines and will therefore have the potential to improve the overall public health of England in the foreseeable future.

The proposed analyses are in keeping with statistical analyses conducted in other similar large-scale population-based studies [45-47]. As the NHS Health Check program collects simple lifestyle-related data, a proportion of the population from this study will be investigated using the NDNS database to derive a more detailed understanding of the impact of nutritional determinants on CVD [48-50]. As this study aims to provide current estimates of CVD risk factor burden in a very large sample of ethnically diverse individuals in London (and following successful linkage with outcomes databases, estimates of association), we believe that this project surpasses every other contemporary study in terms of both its scale as well as representativeness (from an ethnic perspective). While our estimates of association and risk prediction derived from this cohort of CVD-free individuals (at baseline) may be similar to those already obtained from studies conducted in predominantly Western populations, these estimates will nevertheless be significantly refined across diverse ethnicities given the power and precision afforded by the study.

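### The 15,000 expected CVD events do not follow from a 2.4% incidence in 200,000 people, and a flat 100% power for relative risks of 1.2-1.5 does not hold for uncommon exposures

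*Protocol article*

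**What the plan says.** The event count and the power statement stand together in the Sample Size section.

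- Sample: "we anticipate that data will be available on approximately 200,000 individuals across London between 2011 and 2017".
- Rate and base: "Extrapolating the current rate of CVD incidence (2.4%) for people aged below 79 years in England on our estimated study sample of 200,000".
- Result: "we expect to encounter 15,000 CVD events giving 100% power to observe relative risks as modest as 1.2-1.5".
- Subgroups: "Within population subgroups, the power to detect overall association is expected to range from 49% to 100" per cent.

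The section gives no time unit for the 2.4%, no follow-up time behind the 15,000, and no alpha, exposure prevalence or subgroup size. Follow-up is described elsewhere. Study Design and Setting speaks of linkage to "secondary care (hospital) data over 10 years starting in 2009". Statistical Analyses plans "improved risk prediction tools for primary prevention of CVD using outcomes data up to 2020", with recalibration on outcomes to 2027. The Discussion later says that the study's power and precision will refine estimates of association and risk prediction across ethnicities.

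**The concern.** The rate, the base and the result are printed in one sentence, and they disagree by a factor of about three. The count is the stated basis for the overall power claim. It is also the only event count given for the association analyses and for the new prediction tools.

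These analyses are meant to be read by ethnic group, which divides the events further. Some listed predictors may also be uncommon, for example stage 4 or 5 kidney disease, atrial fibrillation and rheumatoid arthritis. A reader deciding which ethnic-specific associations the data can support needs an event count that can be traced, and a power statement that varies with exposure prevalence. The section gives neither.

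**Working it through.** **Inputs from the article.** N = 200,000; rate r = 0.024; stated events 15,000; relative risks 1.2 and 1.5; entry 2011-2017 (Sample Size); outcomes to 2020 and Cox regression (Statistical Analyses); linkage completed by March 2020 (Results).

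**Assumed, because not stated.** Two-sided alpha 5%; exposure prevalence p from 1% to 50%; for the annual reading, entry uniform from the start of 2011 to the end of 2017.

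**Step 1: the plan's own figure.**
- 200,000 × 0.024 = 4,800. The stated 15,000 is not reproduced.
- 15,000 / 200,000 = 7.5%.
- 15,000 / 4,800 = 3.125.

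**Step 2: the rate read as annual.** With follow-up running from t1 to t2 years across entrants, the expected events are N × {1 − [exp(−r·t1) − exp(−r·t2)] / [r(t2 − t1)]}.
- Outcomes to March 2020, t from 2.25 to 9.25: 200,000 × [1 − (0.9474 − 0.8009)/0.168] ≈ 25,600.
- Outcomes to December 2020, t from 3 to 10: 200,000 × [1 − (0.9305 − 0.7866)/0.168] ≈ 28,700.
- Simple multiplication by mean follow-up gives 200,000 × 0.024 × 5.75 = 27,600 and 200,000 × 0.024 × 6.5 = 31,200, which is no closer to 15,000.
- Ten full years for everyone: about 42,700 (exponential) to 48,000 (linear).
- Follow-up cut at the end of the 2011-2017 window, mean 3.0 to 3.5 years: 13,733 to 15,897 (exponential) or 14,400 to 16,800 (linear). This brackets 15,000.
- Exactly 15,000 by simple multiplication needs 3.125 years per person, a figure that the article does not state.

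**Step 3: overall power.** Power = Φ(√(E·p(1−p)) × ln RR − 1.96), where E is the number of events.

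Example: E = 15,000, p = 0.02, RR 1.2. √(15,000 × 0.0196) × 0.1823 = 3.126, and Φ(3.126 − 1.96) = 87.8%.

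| Exposure prevalence | RR 1.2, 15,000 events | RR 1.2, 4,800 events | RR 1.5, 15,000 events | RR 1.5, 4,800 events |
|---|---|---|---|---|
| 20% | about 100% | 99.9% | about 100% | about 100% |
| 10% | about 100% | 96.6% | about 100% | about 100% |
| 5% | 99.8% | 78.6% | about 100% | about 100% |
| 2% | 87.8% | 42.4% | about 100% | 97.6% |
| 1% | 60.3% | 24.1% | 99.9% | 79.8% |

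At 50% prevalence all four columns exceed 99.9%.

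**Step 4: subgroup floor, conditional only.** Suppose the 49% was built on 15,000 total events and the true total is 4,800. Events then shrink to 4,800/15,000 = 0.32 of the assumed number. The noncentrality at 49% power is 1.96 − 0.025 = 1.935. Multiplied by √0.32 = 0.566 it becomes 1.095, and Φ(1.095 − 1.96) ≈ 19%.

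**The case against.** The strongest reply is that 2.4% may be an annual rate. On that reading 4,800 is one year's events, and the planned outcomes to 2020 would yield more than 15,000, so the plan would be conservative. This stands as far as it goes. A reader might infer that the count is overstated three-fold and that both power figures are therefore too high. The article does not establish this, because the time unit is missing and the two readings point in opposite directions.

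An annual rate with follow-up ending in 2017 also brackets 15,000. That may be how the figure arose, but Sample Size names no such cut-off and Statistical Analyses uses outcomes to 2020. The 15,000 is also not far from 2.4% of the eligible pool (587,273 × 0.024 = 14,095). That too is a guess, not evidence of what was done.

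Two further limits stand. First, for common exposures the power claim survives even 4,800 events. Second, the 49-100% range cannot be recomputed, because subgroup sizes, events, relative risks and alpha are not given and the article does not say that it was built on 15,000 events.

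One might also set the subgroup floor of 49% against the Discussion's sentence "given its sample size, our study will have sufficient power to investigate CVD risk factor burden across diverse ethnicities". That sentence concerns risk factor burden, a cross-sectional aim that depends on the number of people and not on events, so it is not contradicted. Only the later claim of power and precision for associations and risk prediction is affected.

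Finally, the 2.4% refers to people below 79 in England, whereas Health Check invitees are aged 40-74 without CVD, diabetes or hypertension. This may lower events. The broad outcome list, with heart failure, all CVD hospitalizations and all-cause mortality, may raise them. The net effect is unknown.

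**Conclusion.** The point holds in a limited form. The 15,000 is not derivable from the rate and sample printed beside it, and neither a cumulative reading nor an annual reading over the stated follow-up gives it. It is about three times too high if 2.4% is cumulative (4,800). It is roughly half of the expected number if 2.4% is annual with outcomes to 2020 (25,600-28,700, assuming uniform entry over 2011-2017).

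Whether or not 15,000 is right, it does not give 100% power throughout the stated range. For relative risk 1.2 it gives about 88% at 2% prevalence and 60% at 1%. On 4,800 events the shortfall extends to 5% prevalence (79%). These power figures rest on an assumed two-sided 5% alpha and the Schoenfeld approximation. A fall in the subgroup floor from 49% to about 19% is conditional on both premises in Step 4 and is not a finding in itself.

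**What to change.** In the Sample Size section:

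1. State whether 2.4% is annual or cumulative, and the follow-up over which it was applied.
2. Rederive the expected events from that rate, the 200,000 and the planned outcome horizon, and show the multiplication.
3. Replace the single 100% figure with power, or minimum detectable relative risk, by exposure prevalence and by ethnic group on the corrected count, stating alpha.
4. Recheck the 49-100% subgroup range against that count, and state the subgroup sizes and relative risk behind it.

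In the Discussion, align the claim of power and precision for associations and risk prediction across ethnicities with the result. The sentence on risk factor burden can stand.

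The cost is recalculation and rewording. No data or participants are added. The stated power may become less favourable.
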